#### Intervention

4.3.2

Participants will receive their usual care plus eight sessions of adjunctive telephone adherence therapy delivered twice weekly for 4 weeks. Each session will last approximately 30 min. FA will deliver adherence therapy under the supervision of RG and DB.

#### Data collection

4.3.3

Before participating in the study, an online baseline assessment questionnaire will be sent. The questionnaire will consist of demographic information, beliefs about medication and medication adherence. Also, included in the demographic information will be questions about their current medication regimen and their most recent HbA1c level. To check the accuracy of self‐reporting, participants answers will be checked with the details of prescribed medication provided in the medical records. The aim of the baseline assessment is to check the validity of self‐reporting and if an online questionnaire is appropriate for this patient group. FA will also interview participants at the end of therapy. The interview will be via phone, last approximately 30 min and will focus on our approach to recruitment, the appropriateness of the measures and the acceptability of the therapy. Interviews will be transcribed and subject to thematic analysis using the approach originally described by Braun and Clark (Braun & Clarke, 2006).

#### Findings

4.3.4

The research team will meet to consider any changes that need to be made based on our findings. Any changes that may be required to the feasibility trial methodology as a consequence of this process will be submitted to the appropriate ethical committee and trial steering committee for review.

### Part two: Feasibility trial

4.4

This study is a parallel‐group open‐label trial to test the feasibility of conducting a full randomized control trial of adherence therapy in patients with type 2 diabetes in a Middle Eastern context. According to the National Institute for Health Research (NIHR), a feasibly study is designed to check if the main randomized control trial can be completed. Some of the possible objectives of a feasibility trial are to estimate the number of eligible patients and the likely recruitment rate (NIHR, 2019). This protocol adheres to the SPIRIT guidelines (A.‐W. Chan et al., 2013) for clinical trial protocols.

### Objectives

4.5

In this trial, we aim to establish whether patients:

Can be recruited to the trial.Complete treatment (at least five out of eight sessions) with telephone‐delivered adherence therapy.Complete study measures using an online web‐based data entry system (RedCAP).

### Study setting

4.6

The study will take a place at the National Guard Hospital, Riyadh, Kingdom of Saudi Arabia. The hospital is one of the largest hospitals in Saudi Arabia with 1,505 beds employing 4,000 nurses and 1,600 physicians. The hospital provides inpatient and outpatient services primarily to people who work for the Saudi Arabian National Guard and their families. A full complement of tertiary services are also provided to the wider regional population (Division of Endocrinology, n.d.).

Participants will be recruited from the diabetes outpatient clinic. The clinic is led by a group of consultants, nurses and other clinicians who assess and review patients and amend their medication or treatment as required. Diabetes educators, predominantly nurses and dietitians, meet with patients to review their medication and provide diabetes education. Patient education is essentially instructional in nature; patients are given factual information by the educators. There is minimal opportunity for discussion between the educator and patient. The clinical service sees around 100 patients with type 2 diabetes a week.

### Eligibility criteria

4.7

Patients will be eligible to participate in this trial if they meet the following criteria.

#### Inclusion criteria

4.7.1

Adults over the age of 18 years.Diagnosed with type 2 diabetes for at least one year.Prescribed any oral or self‐administered injectable medication for the treatment of diabetes (e.g. metformin, insulin).Are non‐adherent to prescribed medication (defined as a Medication Adherence Reporting Scale [MARS] score < 5).

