#### Patient's adherence

To determine patient adherence, we will use the Medication Adherence Reporting Scale (MARS‐5) that was initially developed and validated by (A. H. Y. Chan et al., 2020). The questionnaire has five Likert scale items, for each item answer categories ranging from 1 least adherent to 5 most adherent. The MARS scale was translated and validated in Arabic (Alsous et al., 2017) and has been used to determine adherence in patients with diabetes (Borgsteede et al., 2011; de Vries et al., 2014).

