#### Recruitment

4.10.3

Recruitment of participants will be undertaken at the outpatient clinic of the National Guard Hospital. Approximately 100 patients with type 2 diabetes are seen each week. We estimate that approximately 50% of patients will be non‐adherent according to our definition (i.e. MARS score ≥ 5). In previous adherence studies, around six patients need to be asked to get one to consent (Chien et al., 2015). This means that we can realistically expect to recruit around four patients per week to the trial. Recruitment can be expected to be completed within 5 weeks. Our recruitment will follow the following process:

Step one (checking eligibility): the treating team working in the diabetes clinic will have access to a list of patients who will be seen in the clinic each day. They will undertake an initial screen (i.e. determine they are over 18 years of age and have a diagnosis of type 2 diabetes).Step two (consent to approach): a member of the treating team will then ask patients if they would be interested in taking part in a research project about adherence to diabetes treatment (consent to approach). If they say yes, they will be given a patient information sheet and ask the patient to complete the MARS. At this time, patients will also be told that only patients who regularly miss their medication will be included in the study. Patients who score below seven on the MARS will be informed they meet inclusion criteria and be asked to provide consent. Adherent patients (i.e. those with a MARS score above eight) will be informed that “because adherence does not seem to be a problem for them, they may not benefit from the intervention and on this occasion cannot be included.” Information about the number of people who receive study information and who consent to be approached will be recorded.Step three (informed consent): from patients that meet study inclusion criteria, we will seek online informed consent. FA will explain study procedures and answer any questions participants may have. Participants will have 48 hr to consider taking part in the study at which point online informed consent will be obtained.

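### The MARS cut-offs for non-adherence conflict between the inclusion criterion, the recruitment estimate and the screening step, and no scoring of the five items reconciles them

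*Protocol article*

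**What the plan says.** All references are to the protocol article.

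- **Section 4.7.1, Inclusion criteria.** Patients must be non-adherent, "defined as a Medication Adherence Reporting Scale [MARS] score < 5".
- **Section 4.10, List of measures, Patient's adherence.** The instrument is the five-item MARS: "The questionnaire has five Likert scale items, for each item answer categories ranging from 1 least adherent to 5 most adherent". Whether the score is a sum or a mean is not stated.
- **Section 4.10.3, Recruitment, estimate.** About half of clinic patients are expected to be non-adherent "according to our definition (i.e. MARS score ≥ 5". No source or other cut-off is given for the 50%.
- **Section 4.10.3, step two, acceptance.** "Patients who score below seven on the MARS will be informed they meet inclusion criteria".
- **Section 4.10.3, step two, rejection.** "Adherent patients (i.e. those with a MARS score above eight" are told that adherence does not appear to be a problem for them and are not included. Scores of 7 and 8 are not mentioned.

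**The concern.** The trial is meant to enrol 40 non-adherent patients, and the MARS cut-off is the only rule that separates them from the rest of the clinic. The same rule is given with different numbers in different places, and once in the opposite direction. Staff who follow different sentences will enrol different people.

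In a feasibility trial this bears on the result itself. Section 4.9.1 counts how many patients must be asked to obtain one consent. Step two asks patients first and applies the MARS afterwards, so the cut-off decides how many of those asked can go on to consent. A figure obtained under an unclear cut-off is hard to carry into the design of the main trial.

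**Working it through.** **Inputs.** Five items, each scored 1 to 5, low meaning least adherent (section 4.10). Rules: < 5 is non-adherent (4.7.1); ≥ 5 is non-adherent (4.10.3, estimate); < 7 is accepted and > 8 is rejected as adherent (4.10.3, step two). Recruitment forecast: about 100 patients a week, 50% non-adherent, six asked per consent, target 40.

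**Step 1: a check that needs no scoring assumption.** The sets < 5 and ≥ 5 do not overlap and together cover every number. They cannot both define non-adherence on any numeric score.

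**Step 2: each rule under each plausible scoring.** A sum runs from 5 × 1 = 5 to 5 × 5 = 25, which gives 21 attainable totals. A mean runs from 1 to 5 in steps of 0.2, also 21 values.

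| Rule | Sum, 5 to 25 | Mean, 1 to 5 |
|---|---|---|
| < 5 (inclusion) | none of 21 | 1.0 to 4.8 (20 of 21) |
| ≥ 5 (estimate) | all 21 | 5.0 only, perfect adherence |
| < 7 (accepted) | 5 and 6 | all 21 |
| 7 to 8 (unassigned) | 7 and 8 | none |
| > 8 (rejected as adherent) | 9 to 25 (17 of 21) | none |

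Two other codings were tried:

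- Items recoded 0 to 4 (range 0 to 20) make every cut-off attainable. But < 5 gives 0 to 4, ≥ 5 gives 5 to 20 and < 7 gives 0 to 6, so the conflict stays, and the coding contradicts section 4.10.
- Items dichotomised (range 0 to 5) make > 8 impossible and < 7 universal.

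**Step 3: which scoring lets step two work.** With items scored 1 to 5, a mean cannot reach seven or eight. Of the two, only the sum lets the screening cut-offs separate patients. On the sum:

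- Totals 5 and 6 are accepted at step two, yet each fails < 5, so each such patient violates section 4.7.1 as written.
- A patient answering 2 on all five items, next to least adherent throughout, totals 5 × 2 = 10. Since 10 > 8, this patient is turned away as adherent.
- The lowest rejected total, 9, is an item mean of 9 / 5 = 1.8.

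**Step 4: the 50% share and the forecast.** The plan's inputs give 100 × 0.50 / 6 = 8.3 recruits a week and 40 / 8.3 = 4.8 weeks, which matches the stated five weeks. (The stated rate of about four a week does not follow from these inputs; that is a separate matter.) On a summed score, < 5 gives a share of 0% and no recruits, while ≥ 5 gives 100% and 100 × 1 / 6 = 16.7 a week. Neither is the assumed 50%.

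**The case against.** Several points for the plan are fair, and they limit what can be claimed.

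- **The sum is inferred.** On an item mean, < 5 is attainable and means anything short of perfect adherence. A reader might infer that section 4.7.1 is impossible outright and that the trial would enrol nobody. The article does not support that: impossibility depends on summing, and even then step two would let in totals of 5 and 6. But the mean saves 4.7.1 only by making step two accept everyone, so it does not remove the conflict.
- **The statements are not four rival definitions.** Below seven and above eight are two ends of one screening rule with a gap. Only ≥ 5 runs in the opposite direction, and it may be a slip of the sign for < 5. Correcting that sign would still leave < 5 against < 7, and 7 and 8 unassigned.
- **The 50% is not excluded under every rule.** On a sum it fits neither < 5 nor ≥ 5. For below seven, no MARS distribution is given, so 50% cannot be tested. On a mean, < 5 could give 50%.
- **Counts of scores are not counts of patients.** Of the 3,125 possible response patterns, 3,069 total above eight. A reader might infer that about 98% of patients would be turned away, but patients are not spread evenly over patterns.
- **Not every feasibility outcome is touched.** Interest in the study is expressed before the MARS is completed, and the eligible fraction is not itself a listed outcome.

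The article is a condensed account, but condensing explains missing detail, not statements that contradict one another.

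**Conclusion.** Wrong as written. Sections 4.7.1 and 4.10.3 give conflicting cut-offs, and no scoring of the items described in section 4.10 reconciles them. That conclusion needs no assumption, because < 5 and ≥ 5 are complements.

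The sharper consequences (an unattainable inclusion criterion, a definition that covers everyone, and clearly low scorers rejected as adherent) rest on a summed score. The article does not state this scoring, but the step-two cut-offs imply it. On that reading, the eligible share is 0% or 100% depending on which of < 5 and ≥ 5 is followed, against an assumed 50%. The share under below seven, and the number of patients misclassified, cannot be computed from the article. What is affected is who is enrolled and the number asked per consent.

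**What to change.** 1. State in section 4.10 whether the MARS score is the sum or the mean of the five items, and its range.
2. Reconcile sections 4.7.1, 4.10 and 4.10.3 to one cut-off chosen by the sponsor, with every attainable score in exactly one class. Use it in the inclusion criterion, the recruitment estimate and both halves of step two.
3. Justify the 50% share for that cut-off, or re-derive it, and update the recruitment forecast. The article gives no basis for the present figure, so the cut-off cannot be read back from it.
4. Check that the clinic screening form, the eCRF and the registration carry the same rule before screening begins. They are not shown here and may already be correct.

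The cost is a wording amendment through both ethics committees, with no extra patients or procedures. The forecast may become less favourable once the share is tied to a real cut-off.

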#### Exclusion criteria

4.7.2

Are participating in any other clinical trial.Are currently receiving any other psychological or psychosocial intervention (either face‐to‐face, telephone or online) as this may contaminate treatment effects.Have a terminal illness likely to lead to death within the study period.Have any of the following long‐term conditions: brain injury, psychosis, dementia, cognitive impairment or memory problems. We are excluding these patients as these co‐morbid conditions may make it difficult for the patients to engage in treatment.Are hearing impaired, as the programme is delivered via phone and requires the participants to communicate verbally.

### Interventions

4.8

#### Treatment as usual

4.8.1

Participants in the control and experimental groups will continue receiving their usual care. Treatment as usual for adults with type 2 diabetes includes regular doctor visits and meeting with the health educator if referred by the doctor. Meeting with the diabetes educator includes reviewing the patient's glycaemic control tests, glucose monitoring and a 20‐min didactic educational session.

#### Adherence therapy

4.8.2

A manualized intervention, adherence therapy aims to enhance medication adherence by discussing and carefully challenging patients’ beliefs about medication (e.g. I don't need to take medication if I have no symptoms) and exploring ambivalence about taking medication for diabetes (Gray, 2011). There is also a focus on addressing practical problems (e.g. I forget to take medication) in the adherence therapy approach (Alhalaiqa et al., 2013; Gray et al., 2016). Participants receiving adherence therapy will be sent a SMS about the date/time of the session a day in advance.

In this trial, adherence therapy will be delivered over the phone by FA, a Saudi diabetes educator who trained at the National Guard Hospital. FA will be trained to deliver adherence therapy by RG who initially described the intervention. Training will include a combination of online courses and weekly one‐hour training sessions with RG. In total, FA will attend 12 hr of training. FA will also receive fortnightly supervision from RG and/or DB.

To determine fidelity with adherence therapy, a sample of ten randomly selected sessions will be audio recorded and rated using the Adherence Therapy Scale (ATS) (Gray et al., 2006). Participants will indicate on the consent form if they are willing to have sessions recorded. Not agreeing to have the session audio recorded will not preclude people from participating in the trial.

### Outcomes

4.9

#### Primary outcome (feasibility)

4.9.1

The primary outcome of this trial is the feasibility of recruiting people diagnosed with type 2 diabetes to adherence therapy trial in a Middle Eastern context. Our feasibility outcomes are, therefore, the number of patients:

Asked about the study who express an interest in participating and request further information.That need to be asked to get one to provide informed consent.That complete baseline measures.Who complete treatment (defined as attending five of eight sessions with a session being defined as talking on the phone for at least ten minutes).Who complete postintervention measures.

#### Secondary outcomes (planned outcome measures for the trial)

4.9.2

We will summarize quantitative data using descriptive statistics (mean, standard deviation, 95% CI) outcome measures. They are as follows:

Adherence determined using the MARS.Self‐reported HbA1c.Beliefs about medication, determined using the BMQ.The frequency of missing items across all the measures.

### List of measures

4.10

#### Demographics data

The following demographic information will be collected: age (in years), gender (male, female, other), country of birth, marital status, number of children, highest level of education, city of residence, employment status, family income, duration of diabetes and number of medical comorbidities.

#### Patient's adherence

To determine patient adherence, we will use the Medication Adherence Reporting Scale (MARS‐5) that was initially developed and validated by (A. H. Y. Chan et al., 2020). The questionnaire has five Likert scale items, for each item answer categories ranging from 1 least adherent to 5 most adherent. The MARS scale was translated and validated in Arabic (Alsous et al., 2017) and has been used to determine adherence in patients with diabetes (Borgsteede et al., 2011; de Vries et al., 2014).

#### Patient's beliefs about medication

Patient's beliefs about medicine will be measured using the Beliefs about Medication Questionnaire (BMQ) (Horne et al., 1999). The BMQ is a validated questionnaire that measures beliefs relating to prescribed medication and the patients general view about taking medication. The questionnaire has been translated and validated into Arabic by (Alhalaiqa et al., 2015) and used to measure patients with diabetes beliefs about medication (Schoenthaler et al., 2012; de Vries et al., 2014).

#### Participant timeline

4.10.1

Initial patient screening and consent to approach will be undertaken by the treating team when the patients attend for routine hospital appointments. The researcher will explain the study and obtain online consent within 2 weeks of consent to be approached being obtained (week one). Baseline measures (week two) will be completed within a week of online consent being obtained. Participants will be randomized and informed of group allocation by FA within 2 days of baseline measures being completed. In the intervention group, patients will receive at least weekly sessions of adherence therapy (week three through 12). The intervention will be delivered by telephone and will be no more than 30 min in duration. Treatment will be finished within 10 weeks of the baseline assessment being completed. Patients will be defined as treatment completers if they attend at least five sessions. A completed session is defined as being of at least ten minutes in duration. Qualitative interviews and follow‐up assessments (study end point) will be completed between weeks 13 and 14. The draft CONSORT flow chart can be accessed via Figshare: https://latrobe.figshare.com/articles/CONSORT_feasibility_randomised_controlled_trial_of_adherence_therapy_in_type_two_diabetes_pdf/9724133

#### Sample size

4.10.2

This study will not evaluate the efficacy of adherence therapy; consequently, a formal sample size calculation is not required. There is no clear convention about the number of participants required in a feasibility trial. However, a number of authors have stated that at least 30 participants are required to draw reasonable conclusions about the feasibility of conducting a full trial (Arain et al., 2010; Julious, 2005). Therefore, the sample size in our trial will be 40 patients with a 1:1 randomization ratio.

#### Recruitment

4.10.3

Recruitment of participants will be undertaken at the outpatient clinic of the National Guard Hospital. Approximately 100 patients with type 2 diabetes are seen each week. We estimate that approximately 50% of patients will be non‐adherent according to our definition (i.e. MARS score ≥ 5). In previous adherence studies, around six patients need to be asked to get one to consent (Chien et al., 2015). This means that we can realistically expect to recruit around four patients per week to the trial. Recruitment can be expected to be completed within 5 weeks. Our recruitment will follow the following process:

Step one (checking eligibility): the treating team working in the diabetes clinic will have access to a list of patients who will be seen in the clinic each day. They will undertake an initial screen (i.e. determine they are over 18 years of age and have a diagnosis of type 2 diabetes).Step two (consent to approach): a member of the treating team will then ask patients if they would be interested in taking part in a research project about adherence to diabetes treatment (consent to approach). If they say yes, they will be given a patient information sheet and ask the patient to complete the MARS. At this time, patients will also be told that only patients who regularly miss their medication will be included in the study. Patients who score below seven on the MARS will be informed they meet inclusion criteria and be asked to provide consent. Adherent patients (i.e. those with a MARS score above eight) will be informed that “because adherence does not seem to be a problem for them, they may not benefit from the intervention and on this occasion cannot be included.” Information about the number of people who receive study information and who consent to be approached will be recorded.Step three (informed consent): from patients that meet study inclusion criteria, we will seek online informed consent. FA will explain study procedures and answer any questions participants may have. Participants will have 48 hr to consider taking part in the study at which point online informed consent will be obtained.

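### The stated recruitment rate of four patients per week does not follow from the protocol's own inputs, which give 8.3 per week, and does not fit its 5-week recruitment period

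*Protocol article*

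**What the plan says.** The recruitment projection is in section 4.10.3 (Recruitment) of the protocol article. It gives three inputs:

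- Throughput: "Approximately 100 patients with type 2 diabetes are seen each week". Section 4.6 (Study setting) agrees: "The clinical service sees around 100 patients with type 2 diabetes a week".
- Share eligible on adherence: "We estimate that approximately 50% of patients will be non‐adherent according to our definition".
- Number asked per consent, taken from earlier adherence studies: "around six patients need to be asked to get one to consent".

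It presents the rate as following from these: "This means that we can realistically expect to recruit around four patients per week to the trial". The next sentence gives the duration: "Recruitment can be expected to be completed within 5 weeks".

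Section 4.10.2 (Sample size) fixes the total: "the sample size in our trial will be 40 patients with a 1:1 randomization ratio". Section 4.9.1 makes the feasibility of recruiting the primary outcome, and section 4.13.2 (Governance) has recruitment against target reported to the trial steering committee.

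**The concern.** The rate is offered as a deduction from the three inputs, yet they do not produce it. The rate and the duration stand in adjacent sentences and cannot both hold for 40 patients.

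This matters because section 4.10.3 is the only place where the protocol says how fast patients are expected to join. Section 4.5 lists recruitment first among the objectives, and the Background justifies the study by the risk that a full trial fails to recruit to time and target. Suppose 20 patients have joined by week 5. Judged by the stated rate, accrual is exactly as expected; judged by the stated duration, it is half of what was expected. If this is left unresolved, either description could be given afterwards, and the wrong rate could be carried into planning the full trial.

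**Working it through.** **Inputs**

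- Patients seen per week: 100 (sections 4.6 and 4.10.3)
- Share non-adherent: 0.50 (section 4.10.3)
- Asked per consent: 6 (section 4.10.3)
- Total sample: 40, allocated 1:1, so 20 per arm (section 4.10.2)
- Stated rate: 4 per week; stated duration: 5 weeks (section 4.10.3)

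**Step 1: reproduce the stated rate.** Rate = patients per week × share non-adherent / asked per consent = 100 × 0.50 / 6 = 8.33 per week. The stated 4 is not reproduced. The ratio is 8.33 / 4 = 2.08, too large to be rounding. Taking the factors in the other order (one in six of all patients first, then half of those) gives the same product.

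**Step 2: reproduce the stated duration.** Duration = total / rate.

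| Rate per week | Weeks to reach 40 | Patients in 5 weeks |
|---|---|---|
| 8.33 (from the inputs) | 40 / 8.33 = 4.8 | 5 × 8.33 = 41.7 |
| 4 (as stated) | 40 / 4 = 10 | 5 × 4 = 20 |

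Reaching 40 in 5 weeks requires 40 / 5 = 8 per week. The inputs, the total and the duration are therefore mutually consistent, and the rate of four is the only figure that does not fit.

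**Step 3: see what would make four correct.**

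- As a rate per arm: 8.33 / 2 = 4.17. This matches, but the sentence refers to the trial and not to an arm.
- As a rate for the whole trial: either 50 / 4 = 12.5 patients would have to be asked per consent instead of 6, or only 4 × 6 / 100 = 24% of patients would be eligible instead of 50%. Neither is stated, and either would make recruitment take 10 weeks.

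**The case against.** The best defence of the figure is that the expectation is described as realistic. It may contain an unstated allowance for the other exclusions in section 4.7.2 or for losses between consent to approach and informed consent. That could explain four per week. It could not rescue the paragraph, because the same allowance would make 5 weeks impossible for 40 patients. Nor do the consent and baseline intervals in section 4.10.1 help: they delay entry but do not raise four per week to the eight that are needed.

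The stronger defence concerns the consequence, and most of it stands:

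- A reader might infer that a formal benchmark for the primary outcome is wrong. The documents do not support that. None of the five outcomes in section 4.9.1 is a weekly rate, and no progression threshold is tied to one. Section 4.4 mentions recruitment rate only as a possible objective of feasibility trials. The assumption that does correspond to a listed outcome, six asked per consent, is unaffected.
- A reader might infer that the steering committee has two conflicting formal targets. Section 4.13.2 does not define its target as a rate, and the total of 40 is single and consistent.
- A reader might think the conflict cannot be resolved from the text. In fact the other figures agree and single out four as the outlier.
- A reader might apply the 6.9% to 61.5% non-adherence range from the Background to widen the projection. That is the spread across published studies, which the protocol attributes to measurement problems. The 50% is an estimate under the trial's own definition, so the range has no bearing on this contradiction.

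The sample size is not derived from the rate, and eligibility, allocation and analysis do not use it. The error in the paragraph remains.

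**Conclusion.** The point holds as an internal arithmetic contradiction. The stated rate is lower than the inputs imply by a factor of 2.08, and at that rate the trial would have half of its patients at the end of its stated recruitment period. The most likely explanation is a rate per arm written as a rate for the whole trial. That is an inference, since the text does not say so.

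The conclusion rests only on the protocol's own approximate figures, taken at face value. It does not assume that 50% or six per consent will prove right. The consequence is limited to the planning expectation; no outcome, threshold or analysis is invalidated. It still deserves correction, because the protocol states no other expected rate and recruitment is its primary question.

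**What to change.** Restate the sentence in section 4.10.3 as around eight patients per week in total (about four per arm), with 40 patients recruited in about 5 weeks. This agrees with every other figure in the paragraph and costs one sentence.

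If an allowance for further exclusions or refusals is intended, name it, keep four per week and change the duration to about 10 weeks. The cost is that the stated recruitment period doubles.

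In either case, use that single rate when recruitment is reported to the steering committee. Reporting participants randomized per recruiting week would be a useful addition, but it is optional and the correction does not depend on it.

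### The primary outcome of patients asked per consent does not say who counts as asked, and step two states the adherence rule when it hands out the self-report MARS that decides entry

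*Protocol article*

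**What the plan says.** Recruitment (4.10.3) sets out three steps.

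- **Step one** screens the clinic list on age and diagnosis only.
- **Step two** has the treating team ask these patients whether they are interested in a study about adherence. Those who say yes receive the information sheet and are asked to complete the MARS. The protocol adds: "At this time, patients will also be told that only patients who regularly miss their medication will be included in the study". Patients on the non-adherent side of the cut-off go forward. Adherent patients are told they cannot be included. On record keeping, step two says: "Information about the number of people who receive study information and who consent to be approached will be recorded".
- **Step three** seeks informed consent from those who meet the inclusion criteria.

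Among the primary outcomes, 4.9.1 lists the number of patients "That need to be asked to get one to provide informed consent", without defining the group asked.

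The forecast in 4.10.3 uses these figures: "Approximately 100 patients with type 2 diabetes are seen each week"; "We estimate that approximately 50% of patients will be" non-adherent; "around six patients need to be asked to get one to consent"; and "Recruitment can be expected to be completed within 5 weeks".

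**The concern.** A main trial needs two separate rates from this study: how many clinic patients are eligible, and how many eligible patients consent. Under step two, patients are first asked at a point where nobody knows whether they can join. If that is the asking that 4.9.1 counts, an adherent patient who was willing but turned away weighs the same as a patient who refused. A poor ratio would then not show whether to look for more clinics or to improve the consent approach.

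The second issue is the order of events. The MARS is self-report and decides entry, and the patient hears which kind of answer leads to inclusion at the time the form is handed over. That is an avoidable incentive acting on the eligibility measurement.

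**Working it through.** **Inputs, all from Recruitment (4.10.3) except the target of 40 from Sample size (4.10.2).** Patients seen per week: 100. Non-adherent fraction p: 0.50. Patients asked per consent: 6. Target: 40.

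**1. The plan's own forecast.** Weekly rate = seen × p / asked per consent = 100 × 0.50 / 6 = 8.3. Time to target = 40 / 8.3 = 4.8 weeks, which reproduces the stated 5 weeks. It does not reproduce the weekly rate given beside it ("we can realistically expect to recruit around four patients per week to the trial"): at 4 per week, 5 weeks gives 20 patients, and 40 would take 10 weeks. That mismatch is a separate error. Here it matters only that the 5-week figure fits six per consent applied to the non-adherent half.

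**2. The two readings of the outcome, if everything goes to those assumptions.**

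| Who counts as asked | Asked for 40 consents | Per consent | Consent proportion (exact 95% CI) | Per consent (95% CI) |
|---|---|---|---|---|
| Only MARS-eligible patients | 40 × 6 = 240 | 6 | 16.7% (12.2% to 22.0%) | 4.5 to 8.2 |
| Everyone first asked | 240 / 0.50 = 480 | 12 | 8.3% (6.0% to 11.2%) | 8.9 to 16.6 |

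The intervals are Clopper-Pearson limits for 40/240 and 40/480, inverted. They do not overlap, so the choice of reading matters more than sampling error at this size.

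**3. How the pooled ratio moves with eligibility.** With willingness fixed at one in six eligible patients, the pooled ratio is 6/p: 20 at p = 0.3, 12 at p = 0.5, 8.6 at p = 0.7.

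**4. Whether the pooled ratio can be taken apart afterwards.** Eligible patients asked per consent = pooled ratio × p. An observed 12 fits 3, 6, 9 or 12 eligible patients per consent at p = 0.25, 0.50, 0.75 or 1.0. Without p, that is, without a MARS-eligible count, willingness cannot be recovered.

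**5. Effect of disclosure on the eligible fraction (assumed shifts; the documents give none).** With a true fraction of 50%, the observed fraction is 0.5 × (1 − u) + 0.5 × d. Here d is the share of adherent patients who report non-adherence, and u is the share of non-adherent patients who report adherence.

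- d = 10% to 20%, u = 0: 55% to 60%
- d = 0, u = 10% to 20%: 45% to 40%
- d = u = 10%: 50%, no net change

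The direction and size are open, and the net effect can be zero.

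**The case against.** - **The wording may already mean eligible patients.** Step two says that those who meet the criterion are asked for consent, and step three seeks consent only from them. On that reading the ratio is the eligible-only one and 480/40 never arises. This stands, so the defect is an undefined term and not a wrong definition. It still needs fixing, because the readings differ by a factor of two on the plan's own inputs.
- **The counts may exist elsewhere.** The protocol names two counts at step two without saying they are the only ones, and the draft CONSORT chart it cites is not shown and may separate ineligible from declining patients. This is fair. The chart would not by itself settle which denominator 4.9.1 intends.
- **Six is not a success criterion.** A reader might infer that a trial running to plan would fail its benchmark. The documents do not support that: six is a planning input, nothing judges the outcome against it, and what asking meant in the study it comes from cannot be seen here.
- **The disclosure effect is not demonstrated.** A reader might infer that the eligible fraction is biased. The documents do not show this. The disclosure follows the interest question, so it cannot affect initial interest, and the text does not say whether it comes before or after the answers are written. The eligible fraction is also not a listed outcome in 4.9.1; the number of eligible patients appears only as a general purpose of feasibility trials (Background; 4.4). What remains is an avoidable risk.
- **Early disclosure is transparent.** Telling patients who can join when they get the information sheet is defensible. Delaying it until the MARS result is a trade-off, though adherent patients already receive an explanation at that point.
- **The overall yield has its own use.** If the main trial keeps the same procedure, all patients asked per consent is a valid planning figure. This stands, and it should be reported too.

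**Conclusion.** The point holds as an ambiguity in a primary outcome together with an avoidable risk in the order of step two. If all patients first asked are counted, the protocol's inputs give 12 per consent (8.9 to 16.6); if only MARS-eligible patients are counted, they give 6 (4.5 to 8.2). These figures assume 50% non-adherence, and one in six consenting among the non-adherent, which is the application that reproduces the 5-week duration. The pooled ratio alone cannot separate ineligibility from refusal. No size or direction can be put on the effect of the disclosure. The change is a worthwhile, inexpensive improvement; the documents do not show that the trial would mislead without it.

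**What to change.** 1. **Reconcile the MARS cut-off first.** Inclusion criteria (4.7.1) define non-adherence as below 5. Recruitment (4.10.3) gives 5 or more for non-adherence in the forecast, below seven for inclusion and above eight for adherence in step two. Until these passages agree, MARS-eligible patients cannot be counted.
2. **Reorder step two.** Have the MARS completed before the adherence requirement is stated, and give that explanation with the result.
3. **Tally five counts in sequence:** asked, interested, MARS completed, MARS-eligible, consented.
4. **Define the primary ratio in 4.9.1** as MARS-eligible patients asked per consent. Report beside it the overall number asked per consent and the MARS-eligible percentage among those who completed the form.

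**Cost.** A change to the clinic script, and to the information sheet if it states the rule; a few tallies, mostly from a form already in use; and a formal amendment through both ethics committees (4.13.1). Some adherent patients will complete a five-item form before learning they cannot join, which already happens under the present procedure.
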